## Abstract

**Background:**

Chronic illness is a significant driver of the global burden of disease and associated health care costs. People living with severe chronic illness are heavy users of acute hospital services; better coordination of their care could potentially improve health outcomes while reducing hospital use. The Care Navigation trial will evaluate an in-hospital coordinated care intervention on health service use and quality of life in chronically ill patients.

**Methods/Design:**

A randomised controlled trial in 500 chronically ill patients presenting to the emergency department of a hospital in Western Sydney, Australia. Participants have three or more hospital admissions within a previous 12 month period and either aged ≥70 years; or aged ≥45 years and of Aboriginal or Torres Strait Islander descent; or aged ≥ 16 with a diagnosis of a respiratory or cardiology related illness. Patients are randomised to either the coordinated care program (Care Navigation), or to usual care. The Care Navigation program consists of dedicated nurses who conduct patient risk assessments, oversee patient nursing while in hospital, and guide development of a care plan for the management of chronic illness after being discharged from hospital. These nurses also book community appointments and liaise with general practitioners. The main outcome variables are the number of emergency department re-presentations and hospital readmissions, and quality of life during a 24 month follow-up. Secondary outcomes are length of hospital stay, mortality, time to first hospital re-admission, time to first emergency department re-presentation, patient satisfaction, adherence to prescribed medications, amount and type of in-hospital referrals made for consultations and diagnostic testing, and the number and type of community health referrals. A process evaluation and economic analysis will be conducted alongside the randomised trial.

**Discussion:**

A trial of in-hospital care coordination may support recent evidence that engaging primary health services in care plans linked to multidisciplinary team support improves patient outcomes and reduces costs to the health system. This will inform local, national and international health policy.

**Trial registration:**

Australia New Zealand Clinical Trials Registry ACTRN12609000554268

## Background

Chronic illness is a significant contributor to the global burden of disease, with markedly increasing prevalence and associated stress on health care systems [1]. In Australia, 80% of the estimated total burden of disease is attributed to chronic illness, primarily cardiovascular disease, chronic respiratory conditions, diabetes and cancer [2].

Population ageing exacerbates the burden of chronic disease in developed countries [2]. Health service needs for older populations are complex, involving multiple comorbidities and a broader range of service providers [3]. It is estimated that among independently living Australians, almost half aged 65–74 have five or more chronic conditions, increasing to 70% of those aged 85 and over [4].

People with multiple chronic illnesses are major consumers of health care services [5], accounting for 70% of general practice consultations. They are twice as likely to be admitted to hospital, and stay in hospital disproportionately longer [2]. The substantial cost to government is further challenged by the need to strengthen disease prevention initiatives while providing care to a growing number of patients with chronic disease [6].

High health care costs are driven by the episodic nature of standard health services, which are focused around acute care. This model may be poorly structured and unsupported in the context of patients with chronic illness who can require multiple presentations across private medical specialists, community health, general practice, allied health, and hospital inpatient and outpatient clinics. International research over the past decade suggests that chronic illness may be more effectively treated by better connecting patients’ health management from hospital to community-based services [2,3,5,7-12]. Coordinated care has been identified as a solution which provides this link.

The aim of coordinated (or integrated) care is to enhance quality of care and quality of life, consumer satisfaction and system efficiency for patients with complex, long-term problems across multiple services, providers and settings [13]. Coordinated care can take on a variety of forms, but always involves multidisciplinary communication and care planning [9,14]. Trials to assess the effectiveness of coordinated care have been conducted across the OECD, including in Australia, USA, Canada, England, Italy, Denmark and France [2,3,5,7-12].

A positive effect of community-based care has generally been shown in trials, with lower rates of hospitalisation and lower costs [3,8,10]. Improvements in the level of service access and patient knowledge have also been observed [2]. However, there is inadequate evaluation of the outcomes, and particularly the implementation, of coordinated care interventions within health services. Within the Australian setting, a randomised controlled trial (RCT) of the outcomes of face-to-face coordinated care has not been conducted [2]. More broadly, trials are often focused on specific conditions or population subgroups, and are conducted with small sample sizes and over short timeframes. In addition, trials conducted to date employ a highly variable degree of service coordination.

Solid evidence is required of the effectiveness of care coordination to improve patient outcomes in the population. Implementation of care programs must be evaluated in a way that allows health services to gauge which of its components (e.g., emergency department, wards, discharge, community practitioners) and which of its stakeholders (e.g., patients, carers, nurses, doctors, management, policymakers) facilitate or create barriers to the effectiveness of the new interventions.

### Study objectives

A randomised control trial (RCT) will be conducted to measure the impact of an in-hospital coordinated care intervention, Care Navigation (CN), on health service use and quality of life in elderly and chronically ill patients in Western Sydney, Australia. Effectiveness is based on emergency hospital presentations, hospital admissions and quality of life over 24 months. An economic evaluation examines the cost-effectiveness of CN against current standard care from the perspective of the health sector. A process evaluation will also be conducted to describe the organisational setting and context within which CN has been developed and implemented.

## Methods/Design

### Design and study site

The CN study is a single-blind pragmatic RCT of chronically ill patients presenting to the emergency department of Nepean Hospital. Patients are randomly assigned to receive CN (intervention arm) or standard care (control arm). Recruitment is conducted over 10 months, and the two trial arms are followed for 24 months.

Nepean Hospital is a tertiary teaching hospital in Western Sydney, Australia. It provides inpatient and ambulatory services, and averages 580 overnight beds. In 2009–2010 it provided 28,989 overnight admissions and 19,113 day-only admissions. There were 16,562 medical emergency admissions in that year and a total of 51,414 presentations to the emergency department [15].

### Study participants

The study includes patients identified by an inclusion algorithm implemented within the patient tracking system of the emergency department, or by clinician recommendation. The inclusion algorithm identifies patients who have three or more admissions to a Sydney West Area Health Service hospital within a previous 12 month period and are either aged ≥70 years; or aged ≥45 years and of Aboriginal or Torres Strait Islander descent; or aged ≥ 16 with at least one admission for a respiratory or cardiology related condition. Patients are also eligible if a treating clinician determines that a patient would benefit from receiving CN.

Exclusion criteria are not providing written informed consent; physical or mental inability to give consent or participate in follow-up activities (e.g. dementia); previously received CN; or where language skills prevent questionnaire completion.

### Consent and randomisation

Written informed consent is obtained from all patients. All patients identified by the inclusion screening process are either a) approached in person by a research officer or CN nurse to discuss study participation; or b) approached by telephone, if the patient is identified by the screening process out of hours. All patients approached by telephone are given a patient information sheet while in the hospital, and sign a ‘consent to approach’ form, giving permission for study staff to contact them by telephone.

Randomisation is 1:1 allocation and is conducted using permuted block design and stratified by age group (age ≥ 70, or age ≥ 45 for Aboriginal or Torres Strait islander patients). The randomisation is administered by an independent body (the NHMRC Clinical Trials Centre’s Randomisation Service), who are contacted by telephone for the allocation of each patient to a study arm. Allocation remains masked until after recruitment to the study. Once a participant is randomised, the research officer, the CN nurses and participant are not blinded. The research assistant collecting participant follow-up data remains blind to the treatment allocation throughout the two-year follow-up period. Study statisticians remain blind to allocation until after statistical analyses are complete.

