### Study size

A total of 500 patients are recruited for this study. With an expected 20% loss to follow-up, this results in a final sample size of 400, giving over 90% power to detect a 20% reduction in hospital admissions at a 5% significance level. This effect size is a rate ratio of 0.8 based on an average of 2.5 admissions per patient over a two year period in the control group, compared to 2.0 in the intervention group. The study has more than 80% power to detect a clinically significant difference in ED re-presentations, since ED presentations are more common than hospital admissions. A sample size of 400 would also allow us to detect a mean difference of 10 points on the EQ-5D scale [16], with approximately 80% power at a 5% significance level.

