### Statistical analysis

Cox proportional hazards models are used to analyse time to first ED presentation, time to first readmission and time to mortality. Readmission rates and length of stay are analysed using Poisson or Negative Binomial models. EQ-5D is analysed using analysis of variance, and t-tests for pairwise comparisons. Baseline characteristics, such as age, gender and severity of illness are examined. Model checking of assumptions and good-of fit tests are conducted for all analyses and further analyses are conducted as required. All analyses are conducted according to the intention-to-treat principle, and will be conducted in SAS v9.3.

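### No analysis is stated to include the randomisation stratum or a baseline predictor, and the EQ-5D t-tests cannot, which probably costs precision but not validity

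*Protocol article*

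**What the plan says.** In the protocol article, Consent and randomisation describes 1:1 allocation that is "conducted using permuted block design and stratified by age group". The stratum is age 70 or over, or 45 or over for Aboriginal or Torres Strait Islander patients.

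Study participants sets two entry routes. The screening algorithm requires "three or more admissions to a Sydney West Area Health Service hospital" in a 12-month window, plus an age, Indigenous status or diagnosis condition. The second route carries no count: "Patients are also eligible if a treating clinician determines that a patient would benefit from receiving CN".

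Study variables says the inclusion and exclusion criteria are collected. Table 1 lists EQ-5D at baseline, 12 and 24 months, and age and Indigenous status at baseline. Its hospital data rows cover events during follow-up, and comorbidities come from a 12-month telephone questionnaire.

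Statistical analysis assigns Cox models to the time-to-event outcomes, Poisson or negative binomial models to readmission rates and length of stay, and analysis of variance with pairwise t-tests to EQ-5D. No covariate is attached to any of them. The only reference to baseline data is this: "Baseline characteristics, such as age, gender and severity of illness are examined".

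**The concern.** Stratified allocation balances the stratum between arms, so the treatment estimate varies less than it would under simple randomisation. An analysis that omits a prognostic stratum leaves its variance in the error term and reports a standard error too wide for the design used.

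The same reasoning covers a strong baseline predictor. For admissions, the previous year's count is the most direct marker of risk in the article, and the algorithm already has to compute it. Comorbidities cannot take its place as a baseline covariate, because Table 1 dates them 12 months after entry. For EQ-5D the natural covariate is its own baseline value, which is collected.

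At stake is the precision of primary outcomes. The power for admissions is sensitive to between-patient dispersion, and the two entry routes make a homogeneous population unlikely.

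**Working it through.** **Inputs from Study size and Consent and randomisation**
- Effect size and control mean: "rate ratio of 0.8 based on an average of 2.5 admissions per patient over a two year period in the control group". The mean under Care Navigation is then 0.8 × 2.5 = 2.0, as the article also states.
- 400 analysed (500 less 20%), 1:1, so 200 per arm.
- Significance level 5%, taken as two-sided because the article does not say.
- Stated result: "giving over 90% power to detect a 20% reduction in hospital admissions".

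**Inputs not given, therefore assumed**
- k, the between-patient overdispersion (variance = mean + k × mean²).
- R, the share of k explained by the stratum and prior count.

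**Step 1: reproduce the stated power.** For the log rate ratio,

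SE = √[(1/2.5 + k)/200 + (1/2.0 + k)/200] = √[(0.9 + 2k)/200], and power = Φ(|ln 0.8|/SE − 1.96).

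With k = 0: SE = √0.0045 = 0.0671, and Φ(0.2231/0.0671 − 1.96) = 91.4%. The stated figure therefore reproduces under Poisson variance. Keeping 90% requires (0.9 + 2k)/200 ≤ [0.2231/(1.96 + 1.2816)]² = 0.00474, so k can be at most about 0.024.

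**Step 2: effect of adjustment on admissions.** Adjustment replaces k by k(1 − R), so the SE ratio is √[(0.9 + 2k(1 − R))/(0.9 + 2k)]. Example with k = 0.5 and R = 0.3: √(1.6/1.9) = 0.918.

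| k | Unadjusted SE (power) | Ratio (power), R = 0.1 | R = 0.3 | R = 0.5 |
|---|---|---|---|---|
| 0 | 0.0671 (91.4%) | 1.00 (91.4%) | 1.00 (91.4%) | 1.00 (91.4%) |
| 0.25 | 0.0837 (76.0%) | 0.982 (77.5%) | 0.945 (80.6%) | 0.906 (83.7%) |
| 0.5 | 0.0975 (62.9%) | 0.973 (65.3%) | 0.918 (70.4%) | 0.858 (76.0%) |
| 1.0 | 0.1204 (45.7%) | 0.965 (48.4%) | 0.891 (54.8%) | 0.809 (62.9%) |

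Across k = 0.25 to 1.0 and R = 0.1 to 0.5, the SE falls by 1.8% to 19.1%. At k = 0 it does not fall.

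**Step 3: simulation check.** Counts were generated with log-normal frailty (k = 0.5, 400 patients, 300 runs) and fitted by negative binomial models with and without one baseline covariate. The mean SE ratios were 0.979, 0.956 and 0.908 when the covariate explained 10%, 20% and 40% of the log-frailty variance. The direction agrees with the formula, and the gain is slightly smaller than the formula's 0.973, 0.946 and 0.889 at the same R.

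**Step 4: EQ-5D.** No SD is given. Solving the stated 80% power for a 10-point difference with 200 per arm gives SD = 10/[(1.96 + 0.8416) × √(2/200)] = 35.7. If covariates explain a share R² of the outcome variance, the SE ratio is √(1 − R²). For R² = 0.02, 0.05, 0.10 and 0.20 it is 0.990, 0.975, 0.949 and 0.894, and power is 80.8%, 82.0%, 84.0% and 87.9%. These R² values are also assumptions.

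**The case against.** The strongest reply is that a condensed article names model families and leaves covariates to an analysis plan that is not shown. This largely stands for the count and Cox models. A reader might infer that the trial has decided against adjustment, but the text neither commits to it nor excludes it, and it allows further analyses as needed. The reply is weaker for EQ-5D. Analysis of variance could take the stratum as a factor, but a t-test on the outcome cannot take a stratum or a covariate.

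A reader might also infer that standard errors are too large on every main outcome. The documents do not support that:
- Under the Poisson variance behind the stated power, there is nothing for a covariate to remove.
- Poisson is one of the permitted models. An unscaled Poisson fit to overdispersed counts reports standard errors that are too small, which is the opposite problem.
- In a Cox model, adjustment does not generally shrink the standard error of the log hazard ratio and often enlarges it. Any power gain comes from the conditional estimate moving away from the null.

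Nor can one power gain be claimed. Taking k = 0.5 with 20% to 30% of it removed (k = 0.40 to 0.35) moves power at 400 patients from 62.9% to 67.7% to 70.4%, but neither input is in the article. A gamma-Poisson model limited to patients with at least three prior-year admissions gave lower values: k of 0.26 to 0.31 unadjusted and about 0.20 to 0.23 adjusted. By the Step 1 formula that is power of about 73% to 75% and 77% to 79%. That model implies 3.5 to 6.6 admissions over two years against the planned 2.5, so it does not describe this trial either.

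Finally, the prior count is cut off below three on one route and not required on the other, and recording the inclusion criteria may mean only a threshold flag. That limits its range and completeness as a covariate.

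**Conclusion.** The point holds as one of efficiency. Allocation is stratified, no analysis is stated to carry the stratum or any baseline predictor, and the t-tests named for EQ-5D cannot. Randomisation protects the unadjusted comparison, and leaving out the stratum tends to be conservative, so reading this as bias or an invalid test would go too far.

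The likely consequence is wider standard errors than necessary for EQ-5D and for negative binomial count models. For admissions the reduction available is nil with pure Poisson variance and about 2% to 19% for k = 0.25 to 1.0 with 10% to 50% of between-patient variance explained. For EQ-5D it is about 1% to 11% for R² of 0.02 to 0.20. The article gives neither dispersion nor prognostic strength, so these are ranges under assumption. The direction is firm only where overdispersion exists and the covariates are prognostic. No separate figure can be given for the stratum alone.

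**What to change.** In Statistical analysis, state that:
- the primary models include the randomisation stratum;
- the admission count model, and the count model used for ED re-presentations (the section does not name one), also include the prior-12-month admission count, for example as log(count + 1), and entry route (algorithm or clinician);
- EQ-5D is analysed by a linear model with stratum and baseline EQ-5D, in place of t-tests;
- Cox models may carry the same terms, for power and not for a smaller standard error.

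The cost is a few sentences and one data request. The stratum variables and baseline EQ-5D are already collected. The prior-year count must be extracted as a number, for clinician-referred patients as well as those found by the algorithm. Prior ED visits are not listed among the data collected, so they should be used for the ED outcome only if they can be extracted.

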### Description of the intervention

a) Control arm: current standard care

Patients randomised to current standard care are directed through the hospital system according to the symptoms they exhibit on presentation to the emergency department. This may involve treatment in the emergency department only, or require hospitalisation before discharge. Patients could be linked with hospital and community-based health care facilities, as may normally occur in the absence of CN.

b) Intervention arm: Care Navigation

Care Navigation involves Inbound, Inflight and Outbound care components. The *Inbound* CN nurse receives an electronic page and on-screen alert advising them of an automated referral for a CN consultation at the time of a patient’s presentation to the emergency department. A risk assessment tool to assess the patient’s risk of re-presentation is performed, and a profile of that patient’s health needs is developed and stored electronically, incorporating the patient’s hospital and community health based record, and the patient’s input. Using this profile, the Inbound CN nurse collaborates with emergency medical officers to determine whether the patient requires admission to hospital, or community-based health care. The *Inflight* CN nurse continues patient care after hospital admission. They oversee patient nursing and guide development of a care plan for the management of chronic illness after being discharged from hospital. Patients are care coordinated and/or case managed by the *Outbound* CN nurse, either from the ward or from the emergency department. The Outbound CN nurse collaborates with the patient’s multidisciplinary care team to ensure the patient is ready and safe for discharge, develops community-based care plans, books appointments and contacts general practitioners (GPs). The Outbound CN nurse also makes follow-up phone calls to patients. Care plans are recorded in the patient’s electronic hospital record, faxed to the patients GP, and are revised and updated as required at any subsequent acute hospital presentations and admissions.

### Study variables

In addition to the inclusion and exclusion criteria, six types of variables are collected: demographic and other risk factors, psychosocial, hospital utilisation, community health utilisation, medication usage, and mortality variables. Outcome variables are calculated after 12 months and/or 24 months of follow-up period (Table 1).

**Table 1 T1:** Quantitative data collected in the Care Navigation randomised controlled trial

**Type of data**	**Variables**	**Data source**	**Time of data collection**
**Demographic and risk factor variables**	Age, sex, Indigenous status, marital status	Electronic report from NSW Health database	Baseline.
	Literacy, language, ethnicity, income, education, BMI, living arrangements smoking, alcohol, physical and mental disability, comorbidities	Phone questionnaire-manual data entry	12 months.
**Psychosocial variables**	Quality of life: EQ-5D questionnaire [16]	Phone questionnaire-manual data entry	Baseline, 12 months, 24 months.
	Patient experience: Picker patient experience questionnaire [18]	Mailed paper questionnaire-manual data entry	12 months.
**Hospital utilisation variables**	*For each emergency presentation within the follow-up period:* Triage category, arrival date and time, departure date and time, mode of separation, presenting problem and diagnosis, UDAG status	Electronic report from NSW Health database	24 months.
	*For each hospital admission within the follow-up period:* Arrival date and time, departure date and time, diagnosis related group (DRG), service related group (SRG), investigations conducted	Electronic report from NSW Health database	24 months.
**Community health utilisation variables**	*For each community referral within the follow-up period:* Referral service type, appointment date and time, treatment administered, attendance and transport	Electronic report from NSW Health database	24 months.
**Medication utilisation variables**	Clinical service utilisation (MBS)	Electronic report from Statistics Medicare Australia	24 months.
	Pharmaceutical utilisation (PBS)	Phone questionnaire (manual data entry)	Baseline, 12 months, 24 months.
	Adherence to medications [19]		
**Mortality data**	Date of death	Electronic report from the National Death Index (Australian Institute of Health and Welfare)	24 months.

The three primary outcome measures are a) the rate of re-presentations* to the emergency department; b) the rate of hospital re-admissions*, and c) quality of life. Secondary outcome measures are the length of hospital stay, mortality rates, time to first hospital re-admission, time to first ED re-presentation, hospital key performance indicators, patient satisfaction, and adherence to prescribed medications.

*Includes presentations and admissions to any Western Sydney or Nepean Blue Mountains Local Health District hospital.

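### Three unranked primary outcomes, with the full 5% used for each printed significance level: if any one suffices, the chance of a false significant primary result is about 12–14%, and more if EQ-5D is also tested at 12 months

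*Protocol article*

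**What the plan says.** **Outcomes.** Study variables states "The three primary outcome measures are a) the rate of re-presentations" to the emergency department, then adds the readmission rate and quality of life. The three have equal standing. Study objectives also bases effectiveness on all three, without an order.

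**Significance level.** Study size gives three power statements:
- Admissions: 400 patients, "giving over 90% power to detect a 20% reduction in hospital admissions at a 5% significance level". The assumption is printed: "This effect size is a rate ratio of 0.8 based on an average of 2.5 admissions per patient over a two year period", against 2.0 in the intervention group.
- ED re-presentations: "The study has more than 80% power to detect a clinically significant difference in ED re-presentations". No significance level and no effect size are given.
- EQ-5D: "A sample size of 400 would also allow us to detect a mean difference of 10 points on the EQ-5D scale", "with approximately 80% power at a 5% significance level". No standard deviation and no visit are given.

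**Time point.** A general sentence in Study variables says "Outcome variables are calculated after 12 months and/or 24 months of follow-up period" and points to Table 1. The table extracts ED and admission data at 24 months and collects EQ-5D at baseline, 12 and 24 months. The Abstract and Study objectives place all three primary outcomes over 24 months.

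**Analysis.** Statistical analysis plans analysis of variance and pairwise t-tests for EQ-5D, and count models for readmissions. It names no primary EQ-5D visit, no order of testing and no adjustment.

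**The concern.** When several outcomes are primary and each may use the whole 5%, the chance that at least one is significant by luck exceeds 5% unless a rule ties them together. The printed power figures already assume an undivided 5% for two of the three outcomes. A rule added later may therefore not fit them: if it divides the 5%, the stated power falls; if it does not divide it and any one outcome suffices, the error rate rises.

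EQ-5D adds a smaller opening. With two follow-up visits and none named as primary, it could be tested twice. At stake is how much weight a single significant primary result can bear if the other two are null.

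**Working it through.** **Inputs.** From Study size: 500 recruited; "With an expected 20% loss to follow-up, this results in a final sample size of 400", hence 200 per arm under 1:1 allocation (Consent and randomisation); 2.5 versus 2.0 admissions; 5% level. The article does not say whether tests are one- or two-sided, so two-sided is assumed. All correlations below are assumptions.

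**1. Reproduce the plan's own figures.**
- Dropout: 400 / (1 − 0.20) = 500. Agrees.
- Admissions, Poisson with no overdispersion, Wald test of the log rate ratio: variance = (1/2.5 + 1/2.0)/200 = 0.0045; standard error = 0.0671; z = |ln 0.8| / 0.0671 = 0.2231 / 0.0671 = 3.326. Power = Φ(3.326 − 1.960) = Φ(1.366) = 91.4%. This agrees with the stated figure of over 90%.
- EQ-5D power cannot be checked independently because no standard deviation is printed. The stated 80% is taken as given.

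**2. Chance of at least one false significant result, if any one outcome suffices.**
- Three independent tests: 1 − 0.95³ = 14.3%.
- Three tests, ED and admission statistics correlated 0.7–0.8, quality of life weakly correlated with both (−0.2 to 0.3), by simulation: 12.1% to 13.0%.
- Four tests (EQ-5D at 12 and 24 months), independent: 1 − 0.95⁴ = 18.5%.
- Four tests, ED–admission correlation 0.7–0.8, correlation between the two EQ-5D visits 0.5–0.7, quality of life correlated 0–0.2 with hospital use, by simulation: 15.3% to 16.7%.

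**3. Counting only false claims of benefit.**
- Three independent tests: 1 − 0.975³ = 7.3%.
- Four independent tests: 1 − 0.975⁴ = 9.6%.
- With the correlations in step 2: about 6.1–6.6% for three tests and 7.7–8.5% for four.
- The comparator for one two-sided 5% test is 2.5%.

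**4. Power under rules that control the 5%.**
- Bonferroni, or Holm's first step: 0.05/3 = 0.0167, critical value 2.394.
  - Admissions: Φ(3.326 − 2.394) = Φ(0.932) = 82.4%.
  - EQ-5D: 80% power at 5% implies a mean z of 1.960 + 0.842 = 2.802, so Φ(2.802 − 2.394) = Φ(0.408) = about 66%.
- Full Holm lies between these values and the unadjusted ones: 82–91% for admissions, 66–80% for EQ-5D.
- Fixed sequence, admissions then ED then EQ-5D, each at 5%: admissions keep 91.4%. If the tests were independent and ED had its stated floor of 80%, ED would be claimable with probability 0.914 × 0.80 = 73%, and EQ-5D with 0.914 × 0.80 × 0.80 = 58%. Positive correlation would raise both.
- All three required: the error is at most 5%, but the power for overall success is that same 58% under independence. It cannot exceed the power of the weakest outcome, about 80%.

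**The case against.** The strongest reply is that the article is a condensed report. A multiplicity rule may sit in a full protocol or analysis plan that is not shown, so silence on the rule is not itself a fault. That is right. What remains is what the article does print: three equal primary outcomes, and power at an undivided 5% for two of them.

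A reader might also infer more than the text supports:

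- **That any one significant outcome is the stated success rule.** It is not stated. Study objectives joins the three outcomes with "and", which fits a requirement for all three at least as well. Under that reading the error is at most 5% and the issue becomes joint power.
- **That the trial claims 5% overall and misses it.** The article gives 5% only for individual power calculations. It never claims a trial-wide rate.
- **That all three outcomes are stated to be tested at 5%.** The level is explicit for admissions and EQ-5D and only implied for ED re-presentations.
- **That the choice between 12 and 24 months is open for every outcome.** The general sentence summarises a mixed schedule. Table 1, the Abstract, Study objectives and the two-year basis in Study size set the hospital-use outcomes at 24 months. Only EQ-5D has a second follow-up visit.
- **That three primary outcomes cannot each be tested at 5%.** They can, in a fixed sequence or when all three must succeed.

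**Conclusion.** The point holds conditionally. If any one significant primary outcome is enough to claim effectiveness, the chance of at least one false significant primary result is about 12–14%. It is about 16–18.5% if EQ-5D is also tested at 12 months, where the top of the range needs four independent tests. A false claim of benefit is about half as likely in each case.

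These figures assume two-sided tests, 5% for ED re-presentations as well, and the correlations shown. The power figures for admissions also assume Poisson counts without overdispersion. This is worth correcting before results are seen. It does not show that the trial will make an uncontrolled claim, because a rule may exist elsewhere.

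**What to change.** 1. Name the 24-month EQ-5D comparison as the primary quality-of-life analysis and make the 12-month comparison secondary. The hospital-use outcomes need no change of time point.
2. State how the 5% is controlled across the three outcomes, before anyone sees results by arm. Two suitable options:
   - a fixed sequence at 5% each: readmissions (the outcome with the fullest sample size basis), then ED re-presentations, then EQ-5D;
   - Holm across the three.
3. Restate the power for each outcome at the level actually used, and print the level for ED re-presentations.

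**Cost.** This changes wording only; it needs no new patients or data. Under the fixed sequence, admissions keep the Poisson-based 91%, but a null readmissions result stops any confirmatory claim on the other two. Under Holm, each outcome can be claimed without waiting for another, but some power is lost: at worst to about 82% for admissions and 66% for EQ-5D.
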